## Abstract

**Introduction:** Due to the increasing prevalence of obesity, approaches for a more effective treatment especially in the long-term perspective are needed. However, studies on weight loss and maintenance show heterogeneous results with large inter-individual variations. Therefore, it is of interest to identify factors that contribute to inter-individual differences and predict the success of long-term weight management.

**Methods and Analysis:** The primary outcome of the Lifestyle Intervention (LION) Study is to evaluate the effect of two diets (low carb vs. low fat) and two digital counseling tools (newsletter vs. mobile application) on weight maintenance 12 months after weight loss. The identification of predictive factors (e.g., genetic, epigenetic, physiological, psychological) for the success of weight loss and maintenance is a secondary outcome. Men and women with a body mass index (BMI) between 30.0 and 39.9 kg/m^2^, aged 18–65 years, and without severe diseases are considered eligible. After phenotyping (e.g., anthropometry, resting metabolic rate, meal challenges, blood parameters) participants will follow a formula-based, low-calorie diet (LCD) for 8 weeks. In addition, the intake of 200 g raw or cooked non-starchy vegetables are allowed per day. Subsequently, 252 participants will be randomized into one of the four intervention groups (low carb/app, low carb/newsletter, low fat/app, low fat/newsletter) for the 12-month weight maintenance step. The study will be concluded after another 12 months of follow-up. Results should provide indications for successful weight management and give insights into the personalized treatment of obesity.

**Ethics and Dissemination:** This study has been granted ethical approval by the local Ethics Review Committee of the School of Medicine, Technical University of Munich (vote: 69/19 S).

**Trial Registration Number:** This study has been registered within ClinicalTrials.gov (NCT04023942) and the German Clinical Trials Register (DRKS00017819).

## Introduction

The World Health Organization indicates that overweight affects globally 39% of the adult population, whereas obesity affects 13% of adults (1, 2). In Germany, the prevalence of overweight reaches 67.1% in men and 53.0% in women, whereas obesity reaches 18.9 and 22.5% of men and women, respectively (3).

Both overweight and obesity cause pathophysiological changes in the human body, increasing the risk for comorbidities, such as diabetes, cardiovascular diseases, or some cancers (1, 2, 4). Lifestyle based interventions for weight loss are well-established and are widely recommended in guidelines for the prevention and treatment of overweight and obesity (5).

Lifestyle interventions are usually centered around a “one-size-fits-all” strategy, being successful for the short-term (6). However, weight loss largely differs between individuals, and data on long-term weight maintenance have shown that most people regain weight after weight loss (5, 7). Studies have shown that mean weight loss is moderate with large inter-individual differences, ranging from 25 kg weight loss to 5 kg weight gain (8, 9), depending on intervention type and duration. Aspects that may affect inter-individual differences in weight regulation include lifestyle factors, environment, genetics, phenotype, metabolism, and the microbiome (5, 10, 11). There is still limited knowledge on which factors are associated with weight maintenance, and which therapeutic concepts are successful for weight maintenance. Taking this into consideration, innovative therapeutic approaches and guidance of affected people after weight loss are favorable to achieve weight changes in the long term. Therefore, there is an urgent need to identify predictors and concepts for long-term weight maintenance.

Personalization and digitalization of medical treatment are promising trends in the health care system. Although there are several definitions for “personalized nutrition,” personalization itself should incorporate aspects such as individual preferences, requirements, and habits, combined with key characteristics of an individual's phenotype and genotype to obtain an optimally tailored intervention strategy (6, 11). Which determinants can improve the effectiveness of personalized nutrition is current object of research.

Most research in this field is focused on gene-lifestyle interactions. The DIETFITS trial characterized people with obesity based on their genotypes and post-prandial insulin response. The participants were subsequently matched or mismatched to their “optimal” diet, based on their characteristics at baseline. However, no genotype-diet nor diet-insulin interaction was found for weight loss (8). On the other hand, the POUNDS Lost trial, as well as the DIRECT trial, have found that a specific diet can modify the expression of genes related to weight regulation, supporting weight loss and improving glucose metabolism (12). There is further evidence that the presence of specific genotypes might favor a greater reduction in weight and waist circumference (13).

Furthermore, the group of Zeevi et al. was able to integrate sociodemographic and microbiological characteristics to accurately predict the glucose response of an individual to a meal (10). Results of the POUNDS Lost trial reinforces the hypothesis that the gut microbiota plays a role in weight maintenance since it seems to be able to alter parameters of glucose metabolism (14). Fasting plasma glucose seems to be another determinant that should be considered when matching a diet to an individual's characteristics (4), making it a predictor for weight loss maintenance. However, the research around these types of biomarkers is still in the beginnings and has failed to show clinically relevant results (4, 5).

Several trials compared diets for the treatment of overweight and obesity. It is well-known, that a negative energy balance is relevant for weight loss (15). However, it has been shown that the macronutrient composition of a diet does not affect long term weight loss (9, 16). Low carb concepts lead to a greater initial weight loss compared to other dietary regimes, but have no advantages in the long-term. Other studies found out that low carb diets lead to beneficial metabolic changes (17, 18). Overall, it is rather unclear how low carb and low fat concepts compare regarding weight maintenance after weight loss. Therefore, low carb and low fat diet concepts are innovative in the context of weight loss maintenance and are not yet finally proven.

Finally, novel information and communication technologies (ICT) like wearables and mobile applications (apps) with individualized recommendations, self-monitoring features, or feedback systems may be a useful and inexpensive way to improve weight loss maintenance (5, 19). While self-weighing is known to be effective for weight maintenance, little is known as to whether self-monitoring technologies for tracking lifestyle helps people to maintain their weight. New ICTs promise to facilitate individualized communication at a low-cost level (20). Theses digital tools are not yet proven to support weight maintenance after weight loss.

Overall, weight loss maintenance is difficult for most people and there is a lack of evidence to support the hypothesis that a specific macronutrient composition of a diet or that digital tools can improve weight maintenance. Moreover, predictors for personalized dietary recommendations for weight loss and maintenance are still lacking. In this context, the Lifestyle Intervention (LION) Study aims to compare two different diets (low carb vs. low fat) and two digital tools (newsletter vs. app) for long term weight maintenance. Furthermore, genetic, epigenetic, physiological, psychological, and lifestyle predictors for successful weight loss and weight maintenance should be identified. The overall aim is to contribute to the development of a personalized treatment of obesity. A therapeutic approach tailored to the individual and adapted to their genetic background and metabolic conditions may result in greater weight loss success and maintenance in the long-term.

## Methods and Analysis

### Study Design

The LION Study is a 2 × 2 factorial randomized controlled trial in adults with obesity and comprises four steps: screening and baseline phenotyping (step I), a 8-week weight loss intervention (step II), a 12-month weight maintenance intervention (step III), and a 12-month follow-up period (step IV) (Figure 1). Measurements and data collection occur during face-to-face visits at different time points during the study. However, in individual cases (e.g., due to coronavirus pandemic) face-to-face visits can be converted to phone visits, in which self-reported data will be collected instead of measured data (21). Participants will be enrolled for 27 months from screening to final follow-up and will attend seven visits in total: two visits at baseline (month 1) and one visit each at 3, 6, 9, 15, and 27 months.

**Figure 1 F1:**
[figure not shown]
Study design. Numbers indicate measurements performed during the corresponding visit. (1) Screening questionnaire, (2) anthropometry, (3) collection of biomaterial, (4) meal challenge, (5) questionnaires/protocols, (6) vital parameters, (7) resting metabolic rate, (8) magnetic resonance imaging (subgroup), (9) physical functional performance test (subgroup), (10) hand strength measurement, (11) continuous glucose measurement. * Randomization of the test meal and selected measures. The exact time point of measurements marked by a bracket is dependent of randomization.

### Study Setting

The LION Study is a single-site study and takes place at the Human Study Center of the Institute for Nutritional Medicine, School of Medicine, Technical University of Munich, Germany. The first patient was enrolled in July 2019. Date for last patient out is predicted to be not before spring of 2023.

### Eligibility Criteria

Adults aged between 18 and 65 years, with a body mass index (BMI) between 30.0 and 39.9 kg/m^2^, in ownership of a smartphone and without any severe health condition, that may pose risk for the participant and affect the validity of our findings, are considered eligible. Table 1 specifies all inclusion and exclusion criteria. The participants' eligibility is self-reported and is assessed during a preliminary telephone-based screening interview. In exceptional cases, eligibility is assessed based on the judgment of the investigator on a by-case decision. Individuals who meet inclusion criteria (Table 1) are scheduled for a face-to-face visit.

**Table 1 T1:** Main inclusion and exclusion criteria (self-reported, unless otherwise indicated).

Inclusion criteria	• Age: 18–65 years • Body mass index (BMI): 30.0–39.9 kg/m^2^ (at the scale of the study center) • Ownership of a smartphone with an internet connection (checked by the study team) • No active severe disease • Written informed consent
Exclusion criteria^*^	a. Medical conditions • Diabetes mellitus (Fasting plasma glucose >126 mg/dl, determined either by a rapid tester and laboratory findings) • Anemia (Hemoglobin <12 g/dl, determined either by a rapid tester and laboratory findings) • Severe cardiovascular (e.g., angina, myocardial infarction, stroke), liver (e.g., hepatitis B or hepatitis C), kidney and/or respiratory disease • Clinically significant untreated hypertension (measured and evaluated by the study physician) • Neoplasms (e.g., cancer or gastric ulcer) • Inflammatory bowel disease (e.g., Crohn's disease, ulcerative colitis) • Severe infections/inflammations (chronic or at time of recruitment) • Severe mental, behavioral or neurodevelopmental disorders (e.g., eating disorders, severe depression) • Severe diseases of the nervous system (e.g., Multiple sclerosis, Parkinson‘s disease, epilepsy) • Untreated endocrine diseases (e.g., thyroid disease, determined by laboratory findings) • Severe food allergies or intolerances, that are clinically significant • Severe Lipedema, that is clinically significant b. Medication Medications with the potential of affecting weight, energy expenditure, or the participant's judgment ability (such as glucocorticoids, psychoactive medication, or epileptic medication) are not allowed. The decision will take place on a by-case basis after evaluation of type, dose and usage of the medication by the study's physician. c. Other • Pregnancy and lactation (self-reported or determined by a pregnancy test) • Vigorous weight fluctuations (>5 kg) in the last 3 months • Immobility • Surgery in the last 3 months and bariatric surgery • Participation in other intervention studies, which could influence the study outcomes • Carrier of pacemakers • Blood donation or transfusion in the last 3 months

* *In general, a case and/or condition not named specifically is not an exclusion criterion for enrollment in the first instance. However, if a criterion is considered critical in the judgment of the investigator, the participant is excluded. Additionally, a belated inclusion/exclusion is possible depending on the present case. The study physician makes a final decision on a by-case basis, after estimation of the clinical significance*.

Participants undergo clinical examinations during the first two face-to-face visits (Visit 1A and 1B), serving primarily for baseline phenotyping as well as for the detection of potentially unknown exclusion criteria. For preliminary screening, a drop of capillary blood is withdrawn and fasting plasma glucose, as well as hemoglobin levels, are directly measured at the study center to exclude participants with undiagnosed diabetes mellitus (impaired glucose tolerance is accepted) and/or anemia beforehand. Table 1 specifies the threshold values for glucose and hemoglobin. Fasting glucose and hemoglobin levels of capillary blood are analyzed with the rapid tester HemoCue® Glucose 201+ System (HemoCue AB, Sweden) and DiaSpect Tm Analyser (EKF Diagnostic GmbH, Germany), respectively.

### Interventions

#### Weight Loss Intervention

Once the participant is still deemed eligible after baseline phenotyping (step I), the 8-week formula-based low-calorie diet (LCD) starts as weight loss intervention. Formula products (Itrim, Itrim Sverige AB, Sweden) are provided for the participants free of charge and are regularly handed out at pick up appointments. Each meal provides 200 kcal. A total daily calorie intake of 800 kcal exclusively by formula products is predetermined, resulting in four formula products per day. To increase compliance in the weight loss step, an additional daily intake of 200 g raw or cooked non-starchy vegetables is allowed. Due to further consumption of vegetables, the daily calorie intake is higher than 800 kcal, whereby the weight loss step is classified as LCD. During the LCD, participants fill out a food diary to record consumed products including calorie-free beverages (e.g., water, tea, coffee, beverages sweetened with artificial sweeteners) and vegetables and to document well-being or side effects. Furthermore, participants are phenotyped by a continuous blood glucose monitor (FreeStyle Libre Pro, Abbott Diabetes Care Inc., USA) during the first 4 weeks of intervention.

During the weight-loss period, participants are contacted regularly by phone (at weeks 1, 2, 4, and 6) to ensure well-being, to record observed side effects and to increase compliance. After 8 weeks of LCD, participants attend a face-to-face visit (Visit 2) at the study center, which ensures a seamless transition to the weight maintenance step.

#### Weight Maintenance Intervention

In order to exclude participants with either no or low adherence to the formula diet, only participants that achieved a weight loss over 4 kg after 8 weeks of LCD, are eligible for randomization into one of the four weight maintenance intervention arms: (a) low carb and app-based group, (b) low carb and newsletter-based group, (c) low fat and app-based group, (d) low fat and newsletter-based group.

Low carb is defined as 30 energy percent from carbohydrates, 50 energy percent from fat, and 20 energy percent from protein. Low fat is defined as 25 energy percent from fat, 55 energy percent from carbohydrates, and 20 energy percent from protein. This nutrient composition was firstly defined to allow the protein intake of both groups to be standardized and comparable, and secondly, to ensure feasibility and compliance to the weight maintenance diet for the long-term. There is no further breakdown specifying fat or carbohydrate types in the weight maintenance diet. However, participants are trained to make healthier decisions with the help of an overview which foods should be avoided and which better alternatives are available (providing information on e.g., low carb/low fat preparation of food, choosing low energy but nutrient-dense alternatives, or choosing foods with lower fat/lower carb content in the same food group).

The daily energy requirement is calculated for each participant individually, based on the measured resting metabolic rate (RMR) after weight loss multiplied with the individual's physical activity level (PAL). The PAL is chosen based on the PAL values for work and leisure activities of the German Nutrition Society, according to self-reported work, leisure, and physical activities. However, the recommended daily energy intake in the weight maintenance period is 10% lower than the calculated daily energy requirement (recommended daily energy intake = (RMR x PAL) – 10%). The reduction by 10% serves as a safety buffer to ensure weight maintenance, to diminish known inaccuracies in the calculation of energy requirements. If desired, further weight loss is allowed during the weight maintenance step, provided that it is performed within the framework of the weight maintenance intervention. The participant's compliance is estimated based on the recurring determination of blood and urine parameters (e.g., urea concentration for protein intake), and macronutrient composition of total energy intake assessed by a dietary record at three time points during the 12-month weight maintenance step. At months 6, 9, and 15 participants are examined in face-to-face visits (Visit 3A, 3B, and 3C).

Participants assigned to the app-based intervention group, regularly have contact with a coach via the app (Oviva, Oviva AG, Switzerland), providing nutritional guidance and support during the 12-month weight maintenance step. In the beginning, there is a single phone call between coach and participant to get to know each other and to become familiar with the participant's “starting point.” Afterward, conversations between coach and participant take place within the app's private chatroom in a decreasing frequency (weekly in the first 3 months, every 2 weeks in the following 6 months and once a month in the last 3 months of intervention). Additionally, participants are provided with a monthly information sheet (LION-Info) containing information (e.g., recipes, shopping lists, preparation of food) on the assigned diet and tips for long-term weight maintenance. Content to be discussed between coach and participant is standardized by the study team. However, the participant can address specific dietary questions to the coach. All coaches are certified nutritionists and are additionally trained by the study team. Tracking of weight/physical activity and uploading pictures of meals (as a picture-based dietary record) are some examples of further features within the app, which are not mandatory for the intervention but can be additionally used by the participants.

In comparison, participants assigned to the newsletter-based intervention group get digital newsletters regularly via email, providing nutritional information (e.g., recipes, shopping lists, preparation of food, basic nutritional facts, quizzes) regarding the assigned diet in the same frequency as “contacts” take place in the app-based group. Information included in the LION-Info is also provided in the newsletter. However, the newsletter is kept more general, to be appealing to a broader group of people. Content to be discussed in the newsletter is standardized by the study team and is identical to the LION-Info sent to the app-based intervention group.

#### Follow-Up

During the 12-month follow-up, all participants receive a newsletter with general information on self-help for long-term weight maintenance every 3 months, independent of the assigned weight maintenance intervention group. Topics to be mentioned include not only nutritional information, but also refer to psychological aspects and physical activity for weight maintenance. After 12 months, the final face-to-face visit (Visit 4) takes place, concluding the study participation.

### Meal Challenges

For phenotyping purposes and analysis of individual metabolic responses as a secondary outcome, participants take part in two meal challenges at baseline (Visits V1A and V1B). All participants undergo an oral glucose tolerance test (OGTT) and a lipid meal challenge, which itself can be based on a plain lipid drink (oral lipid tolerance test, OLTT) or a glucose-lipid mixed meal challenge (oral glucose and lipid tolerance test, OG+LTT) (Figure 2). Blood is drawn at baseline and several time points after administration of the test drink, to monitor changes of metabolites in the blood (e.g., glucose, insulin, and lipid profile) (**Table 3**).

**Figure 2 F2:**
[figure not shown]
**(A)** First randomization: meal challenges. After the telephone-based screening and before the first visit, the order of meal challenges as well as the type of lipid meal challenge will be randomized. Two meal challenges are carried out per participant (one during Visit V1A and one during Visit V1B). Oral glucose tolerance test (OGTT), oral glucose and lipid mixed meal challenge (OG+LTT), oral lipid tolerance test (OLTT). **(B)** Second randomization: weight maintenance intervention. After weight loss (during the Visit V2), participants are randomized to one of the four intervention groups. The second randomization is stratified according to the parameters of the first randomization. No results of the meal challenge tests (blood and other metabolic parameters) are considered for randomization.

The OGTT is carried out after an overnight fast after consumption of a 300 ml drink providing 75 g glucose. The OGTT-drink is prepared as follows: 82.5 g glucose monohydrate (≥99.5% D(+)-glucose monohydrate, Ph. Eur.; Carl Roth GmbH + Co. KG, Germany) filled up to 300 ml with tepid water. Blood is drawn at baseline and 30, 60, 90, and 120 min after drinking the test meal.

The lipid meal challenge is also carried out after an overnight fast. The type of the administered lipid meal challenge (plain lipid drink or a glucose-lipid mixed drink) is randomly chosen for each participant. The glucose-lipid mixed meal challenge (OG+LTT) is applied as an attempt to modulate different processes of metabolic health in comparison to a plain glucose or plain lipid meal challenge. The OLTT-drink is prepared as follows: a fat emulsion drink (Calogen®, Nutricia GmbH, Germany) is filled up with water to 300 ml. The fat emulsion drink provides 35 g fat per m^2^ of the participant's body surface, which is calculated based on the equation by Du Bois and Du Bois (22). The 300 ml OG+LTT-drink is prepared analogous to the plain lipid drink and contains additionally 82.5 g glucose monohydrate. Blood is drawn at baseline and 30, 60, 120, 180, 240, and 300 min after drinking the test meal.

To guarantee a washout period, without distorting the baseline data, the two first visits (Visit 1A and 1B) should be at least 3 days apart.

### Outcomes

The primary objective of the LION Study is to evaluate the effect of two diets (low carb vs. low fat) and two digital counseling tools (app vs. newsletter) on long-term weight maintenance 12 months after weight loss (weight change from baseline to month 15, Visit 3C).

Secondary objectives are mainly focused on the identification of predictors for the success of weight loss and weight loss maintenance. This includes data such as anthropometric, metabolic, and genetic parameters; RMR; clinical, lifestyle, psychological, environmental, and social factors; adipose tissue and fat compartments measured by magnetic resonance imaging (MRI, subgroup); among others. The characterization of metabolic responses on meal challenges at baseline (Visits V1A and V1B; Tables 2, 3) that may predict the success of weight loss and weight loss maintenance is one of the main secondary objectives.

**Table 2 T2:** Data collection plan.

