### Sample Size and Power Calculation

A total of 252 participants will be randomized to the weight maintenance step (*n* = 63 per arm). Assuming a 30% dropout, there will be 176 participants (*n* = 44 per arm) that provide primary endpoint data. A sample size of 176 participants is sufficient to detect a difference in weight loss maintenance of 1.7 kg between the two dietary intervention arms and the two digital tools with a power of 80%, a significance level of 0.05 and assuming a within-arm standard deviation of 4.0 kg.

To randomize 252 participants to the weight loss maintenance step, it is estimated that 504 participants are needed to be included in the weight loss step. This estimate is based upon the assumption that 30% of participants will drop out during weight loss and that 20% will not reach the weight loss of 4 kg, which is necessary for randomization to one of the four weight maintenance groups. These are conservative estimates for dropout and ineligibility. If these rates are lower, fewer people will need to be screened and included in the weight loss step.

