### Randomization

There are two randomization time points (Figure 2). The first randomization takes place at baseline, shortly before the participant attends the first visit and determines either the order of the two meal challenges (OGTT and lipid meal challenge) as well as the type of the lipid meal challenge (plain lipid drink or a glucose-lipid mixed drink). The second randomization takes place after weight loss during visit V2, in which participants are randomly assigned to one of the four weight maintenance intervention arms. This randomization step is stratified according to the order and type of meal challenges assigned with the first randomization. The results of the meal challenge tests (e.g., glucose response) are not considered for the weight maintenance intervention.

For each randomization, an online tool of the Münchner Studienzentrum (MSZ) is used to generate the allocation sequences. This online tool uses pre-defined randomization lists, created block-wise. Due to the nature of the intervention, it is not possible to blind the participants as well as the study team.

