### Statistical Analysis

To investigate the primary outcome, a comparison of groups in the weight maintenance step (app groups combined vs. newsletter groups combined and low carb groups combined vs. low fat groups combined at month 15) will be conducted based upon a linear regression model. A further regression model assesses a potential interaction between the dietary and mode of delivery interventions. A complete-case analysis and analysis using multiple imputations will be performed. Participants are analyzed according to groups to which they are randomized (intent-to-treat, ITT).

The continuous secondary endpoints at different time points are compared between the dietary and the mode of delivery groups using analogous linear regression models in complete-case analyses.

Exploratory analyses are performed to assess parameters as potential predictors for effective weight loss and weight maintenance. Exploratory analysis can be restricted to subgroups based on a per-protocol analysis. For instance, to address the bias of self-reported data obtained due to the implementation of telephone-based visits during the coronavirus pandemic, the mode of visits will be considered in statistical analysis (e.g., by adjusting according to the mode of the visit). Moreover, interaction terms (e.g., gene-diet interactions) will be considered as exploratory analyses. Since further weight loss is allowed during weight maintenance, weight trajectories during this period will be also one element of subgroup analysis (e.g., weight loss, stable weight, weight regain).

Finally, missing data are a challenge in long-term clinical studies. Depending on the amount of acquired missing data, statistical analysis will be adapted (e.g., imputation).

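### The primary outcome is called weight maintenance after weight loss but is measured from month 1, before randomization at month 3, and the 4.0 kg SD behind the power is tied to neither interval

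*Protocol article*

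**What the plan says.** The Outcomes section of the protocol article describes the primary objective as the effect of two diets and two digital tools on "long-term weight maintenance 12 months after weight loss (weight change from baseline to month 15, Visit 3C".

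The Study Design section fixes the calendar: "two visits at baseline (month 1) and one visit each at 3, 6, 9, 15, and 27 months". The Outcomes section uses the word baseline in the same sense a few lines later: "The characterization of metabolic responses on meal challenges at baseline (Visits V1A and V1B; Tables 2, 3".

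The compared arms do not exist until after the diet. The Randomization section states: "The second randomization takes place after weight loss during visit V2, in which participants are randomly assigned". The Weight Maintenance Intervention section adds the entry condition: "only participants that achieved a weight loss over 4 kg after 8 weeks of LCD, are eligible for randomization".

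The Sample Size and Power Calculation section says that 176 analysed participants suffice "to detect a difference in weight loss maintenance of 1.7 kg" between the two diets and between the two tools, with 80% power, significance level 0.05 and a within-arm SD of 4.0 kg. It does not name the interval over which that SD is taken. For the primary comparison, the Statistical Analysis section says only that it "will be conducted based upon a linear regression model".

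**The concern.** The name of the outcome and its definition point to different intervals. The Discussion places the final visit 24 months after weight loss. That visit is at month 27, so weight loss ends at month 3, and maintenance 12 months later is the span from month 3 to month 15. The definition covers months 1 to 15.

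The difference is the diet phase. Everything lost between V1A and V2 happens before assignment, yet it sits inside the outcome. Three things are at stake:

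- **Interpretation.** A participant who loses 15 kg and regains 5 kg scores the same as one who loses 6 kg and then 4 kg more (both 10 kg below month 1). The endpoint does not separate a regainer from a continuing loser, although the Statistical Analysis section plans to distinguish those trajectories.
- **Precision.** Diet-phase variation may add to the variance of the outcome without carrying any information about the arms.
- **Power.** If the 4.0 kg SD belongs to the maintenance phase, it is not the SD of the endpoint as defined, and the stated 80% does not apply to it.

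**Working it through.** **Inputs from the protocol article.** Difference 1.7 kg, SD 4.0 kg, significance level 0.05 (taken as two-sided; the article does not say), and 176 analysed as 44 per arm, hence 88 versus 88 for each factor. Randomized 252; 252 × 0.70 = 176.4, which matches the 176.

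**Reproducing the stated power.** Standard error = 4.0 × √(2/88) = 0.603 kg. Non-centrality = 1.7 / 0.603 = 2.82. Two-sample t power with 174 degrees of freedom = 80.1% (80.5% by the normal approximation). The stated 80% is arithmetically right for an endpoint whose SD is 4.0 kg.

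**Which endpoint has that SD?** Let L be the change from V1A to V2 with SD s, and M the change from V2 to V3C. The defined endpoint is L + M. There are two readings of the 4.0 kg:

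- *Reading A: 4.0 kg is the SD of L + M.* Power is 80% as stated.
- *Reading B: 4.0 kg is the SD of M.* Then SD(L + M) = √(4.0² + s² + 2ρ × 4.0 × s), where ρ is the correlation of L with M. Because L is a loss and regain is positive, a negative ρ means that larger losers regain more.

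Neither s nor ρ is in the article. Both are assumptions here, shown over a range. The over-4-kg entry rule cuts off the low end of diet-phase loss, which tends to reduce s among those randomized; the article does not allow the amount to be estimated.

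Reading B, outcome L + M, V2 weight not in the model, 88 versus 88. Each cell gives the endpoint SD and the t power for 1.7 kg:

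| s (kg) | ρ = 0 | ρ = −0.3 | ρ = −0.6 |
|---|---|---|---|
| 2 | 4.47 kg, 71% | 3.90 kg, 82% | 3.22 kg, 94% |
| 3 | 5.00 kg, 61% | 4.22 kg, 76% | 3.26 kg, 93% |
| 4 | 5.66 kg, 51% | 4.73 kg, 66% | 3.58 kg, 88% |
| 5 | 6.40 kg, 42% | 5.39 kg, 55% | 4.12 kg, 78% |

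Under independence, the difference detectable with 80% power is 1.9, 2.1, 2.4 and 2.7 kg for s = 2, 3, 4 and 5 kg.

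**When is there no inflation?** SD(L + M) is at most 4.0 when s² + 8ρs ≤ 0, that is, when ρ ≤ −s/8. For s = 2 kg the threshold is −0.25; for s = 4 kg it is −0.50.

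**What adjustment does.** Simulated power with s = 4 kg and an M SD of 4.0 kg (4,000 runs per setting):

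| Model | ρ = 0 | ρ = −0.3 |
|---|---|---|
| Change from V1A, unadjusted | 52% | 66% |
| Change from V1A, adjusted for V1A weight only | 51% | 66% |
| Change from V2, unadjusted | 80% | 79% |
| Change from V1A, adjusted for V1A and V2 weight | 80% | 82% |

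Adjusting for V1A weight alone recovers nothing; V2 weight is what matters. With both weights in the model, the outcomes V3C − V1A and V3C − V2 differ only by a linear combination of covariates, so the treatment estimate and its standard error are identical. Each unadjusted change score is the special case in which the weight coefficients are fixed in advance, so the adjusted residual variance cannot exceed that of either score, apart from the two degrees of freedom spent. For example, at ρ = −0.3 the residual SD is 4.0 × √(1 − 0.09) = 3.82 kg.

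**The case against.** The strongest reply has four parts.

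1. *The wording can be read without contradiction.* The phrase about 12 months after weight loss may say when the outcome is assessed, and the parenthesis may say how. Weight loss maintenance can mean how much of the original loss is still held at month 15, which needs a pre-diet reference. This is a fair reading, and a month-1 anchor is not illegitimate. It remains true that the endpoint then includes change from before assignment, and that a reader expecting post-diet regain will be given a different quantity.

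2. *The comparison is not distorted.* Randomization at V2 balances diet-phase loss in expectation. The between-arm contrast has the same expectation on either anchor, and chance imbalance is carried in the standard error. This stands in full: there is no bias and no inflation of type I error.

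3. *A loss of power is not demonstrated.* A reader might infer that the stated power is lost, or that the variance must be larger on the month-1 anchor. The article supports neither. It does not tie 4.0 kg to an interval, gives no diet-phase SD, and leaves ρ open. With ρ = −0.3 and s = 2 kg the endpoint SD is 3.90 kg and power is 82%, above plan. This stands.

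4. *Covariates may be set elsewhere.* A condensed article commonly leaves them to a fuller protocol or analysis plan, so its silence on V2 weight is not a defect. This also stands. The point rests on the outcome definition and on the unlabelled SD, both of which the article does state.

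**Conclusion.** The concern holds as a matter of definition, precision and interpretation. The primary outcome carries the name of post-diet maintenance, but its reference point is month 1, two months before the arms are randomized, so it includes weight change that no arm can affect.

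The 80% power is correctly computed for an SD of 4.0 kg but cannot be confirmed for the endpoint as defined. The 42 to 71% range requires all of the following: 4.0 kg is the V2-to-V3C SD, V2 weight is left out of the model, the diet-phase SD lies between 2 and 5 kg, and the two phases are independent. Relaxing independence towards greater regain in larger losers shrinks the loss or removes it; at ρ = −0.6 the range is 78 to 94%. If 4.0 kg already describes months 1 to 15, nothing is lost.

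The case for changing the plan does not depend on which scenario is true. Conditioning on both weights makes the choice of anchor irrelevant to the treatment estimate and costs essentially nothing in precision.

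**What to change.** 1. **Outcomes.** Either define the primary outcome as weight change from V2 (randomization) to V3C, with change from month 1 reported as secondary, or keep the month-1 anchor and say explicitly that it includes the diet phase.
2. **Statistical Analysis.** With either anchor, fit one linear model with both factors (diet and tool), V1A weight, V2 weight and the randomization strata (order and type of meal challenge).
3. **Sample Size and Power Calculation.** State the interval to which the 4.0 kg SD refers. If it is not the interval analysed, restate the power.

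The cost is about one sentence in each of the three sections, plus a registry update if the anchor moves. The article's data collection plan already schedules body weight at V1A, V2 and V3C, so no new measurement and no change in sample size is needed for the adjustment itself.
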